Protocol:

**Aim**

To evaluate muscle quality in patients with late onset Pompe disease (PD) in comparison to healthy controls by determining muscle strength in relation to muscle size.

Furthermore, to evaluate muscle quality in patients with late onset PD before and following enzyme replacement therapy (ERT).

To evaluate muscle quality in patients with Dystrophia Myotonica in comparison to healthy controls by determining muscle strength in relation to muscle size.
Compare the findings from the two patient groups.

**Introduction:**

**Pompe Disease**

Pompe Disease (PD), also known as Acid Maltase Deficiency (AMD) or Glycogen Storage Disease type II, is a rare autosomal recessive disorder, caused by lack of the lysosomal enzyme α-glucosidase (AAG). The enzyme is responsible for metabolizing lysosomal glycogen. The lack of the enzyme results in glycogen accumulation within the lysosomes, which ends in cellular damage and tissue damage^[[1]](#endnote-1)^. The estimated frequency of the disease is 1/40,000 in Netherlands^[[2]](#endnote-2)^, and similar or lower frequencies have been reported for other countries^[[3]](#endnote-3)^ ^[[4]](#endnote-4)^.

The disease presents in a wide range of phenotypes, differing in age at onset, severity of symptoms and disease progression. The most severe form is the infantile form, characterized by complete lack of AAG presenting at 1 to 2 months of age. It especially affects the heart and skeletal muscle and death occur before the age of 2 years due to cardiorespiratory failure.

The less severe form, where residual activity of AAG is still detectable, can manifest from young

age to adulthood (late onset Pompe Disease). Symptoms are generally related to skeletal muscle dysfunction, resulting in fatigue, muscle weakness and respiratory deficiency^[[5]](#endnote-5)^ ^[[6]](#endnote-6)^.

**Enzyme Replacement Therapy and disease monitoring**

In 2006 Enzyme Replacement Therapy (ERT) with recombinant AAG was approved for Infantile PD.

Several studies has since shown good therapeutic effect of the recombinant alglucosidase also for late onset PD^[[7]](#endnote-7)^ ^[[8]](#endnote-8)^ ^[[9]](#endnote-9)^.

The main endpoints have been the 6 minute walking test (6MWT) and vital capacity (VC). However, the studies underline the heterogeneity of clinical manifestation of disease and of ERT outcome, and that monitoring of disease progression and effect of ERT is needed.

A new emerging and promising tool for disease monitoring is magnetic resonance imaging (MRI). This technique has been useful in many neuromuscular disorders. The technique is non-invasive, has high spatial resolution and introduces no risk to the patients (especially ionizing radiation exposure). Since MRI has good soft-tissue contrast it is useful for identification of fat replacement in muscles^[[10]](#endnote-10)^ ^[[11]](#endnote-11)^.

**Magnetic Resonance Imaging and Pompe Disease**

In chronic diseases, muscle involvement detected by MRI is based principally on signal intensity changes resulting from fat infiltration into muscle combined with decreased muscle volume. It is therefore possible to observe muscle involvement of the disease, which overall follows a characteristic pattern^[[12]](#endnote-12)^.

In late onset PD Pichiecchio et al., found that the MRI score related to the severity of muscular abnormalities and to the patients’ loss of muscular strength (MRC scale)^[[13]](#endnote-13)^. The same correlation between muscle involvement on MRI and muscle strength was reported by Vielhaber et al.^[[14]](#endnote-14)^ and Alejaldre et al^[[15]](#endnote-15)^.

The research group of Pichiecchio et al. also used MRI to evaluate the effects from 6 months of ERT, and found that ERT results in increased muscle mass, subcutaneous fat and intramuscular fat. Quantitative increase in the muscle bulk was mainly observed in the spared muscle^[[16]](#endnote-16)^.

Moreover it seems that changes in muscle mass positively correlate to changes in muscular strength (measured on hand-held dynamometer), and that those changes can be detected after one year of ERT therapy^[[17]](#endnote-17)^.

A recent Danish study had different findings^[[18]](#endnote-18)^. Interestingly, weak muscles seemed to benefit more from ERT than less affected ones, which is in contrast to previous findings. Furthermore, flexor muscle groups had greater response to ERT, contrasting previous studies reporting greater effect of the extensor muscle groups.

These contradictory findings could be due to differences in design and methodology (for example in measuring muscle strength and choosing different sequences of muscle-MRI) or it could be due to the heterogeneity in the clinical presentation of PD.

Therefore, more studies are needed, in order to determine the relation between the effect of ERT on muscle mass and muscle strength in PD patients.

**Dystrophia Myotonica**

an autos o-

mal dominant multisystemic disorder, is the most

common adult for m of muscular dystrophy, af fect-

ing approximately 1 in 7400

an autos o-

mal dominant multisystemic disorder, is the most

common adult for m of muscular dystrophy, af fect-

ing approximately 1 in 7400

Dystrophia Myotonica is an autosomal dominant progressing multisystemic disease. It is the most common adult form of muscular dystrophy. In Denmark there are approximately 1500 people living with the disease^[[19]](#endnote-19)^.
As with Pompe disease, the muscular tissue slowly degenerate and fat infiltration occur.
As it is the case with other muscular diseases, there is an increasing interest for MR imaging as a useful non-invasive toll for monitoring the disease and for monitoring the outcomes of the increasing numbers of clinical trials on Dystrophia Myotonica^[[20]](#endnote-20)^.

**Hypothesis**

In this study, we want to test the following hypotheses:

- Intrinsic muscle strength in patients with Pompe disease and Dystrophia Myotonica is linear correlated with muscle to fat volume ratios from MR images.
- Disease grade in patients with Pompe disease and Dystrophia Myotonica corresponds to the extent of fat proliferation in the muscles of the lower extremities.
- Intrinsic muscle strength is a more specific and sensitive method to reveal the effects of enzyme replacement treatment in patients with Pompe than the six minutes-walk-test.

**Method**

**Study population**

Pompe disease population

Fifteen patients with PD and 15 healthy age matched control subjects will be included. All patients with PD in Denmark (9) will be invited to participate, irrespective of whether they are given ERT or not. The remaining participants will be recruited among PD patients from the northern part of Germany (the Hamburg and Schleswig- Holstein area). Patients will be evaluated at inclusion and again after 10 months.
In case of de novo patients an additional examination date will be performed following 6 months of treatment. This will provide detailed new results of muscle structure and function in the early stages of treatment, before and after initial ERT. This provides the opportunity to monitor the effects on ERT during the first year of treatment, which is the period where the greatest effect of ERT on muscle strength has been found.

In addition to the MRI and Dynamometer measurement, participants will be evaluated with a 6 min. walking test, vital capacity and negative inspiration/expiration test, sit-to-stand test as well as a structured neurological examination.

Dystrofia Myotonica population

Fifteen patients with Dystrophia Myotonica will be included. Subjects will be recruited via their attendance at the hospital clinic of Aarhus University Hospital.

INCLUSION CRITERIAS

- Diagnosed Pompe disease patients, whether they are in treatment with ERT or not.
- Diagnosed Dystrophia Myotonica patients.
- Healthy controls, have to be age-matched to patients with muscular disease.
- Age above 18

EXCLUSION CRITERIAS

- The subjects must be able to perform an MR-scanning. Moreover they have to sign and respect the MR security rules “Kontrol skema før MR undersøgelse” and "Patient information i forbindelse med MR scanning”
- The subjects must be capable of performing the muscle strength test by the Dynamometer.

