**Statistics**

Comparison between baseline and visits will be performed using conventional statistic methods as unpaired t-test or non-parametric tests such as Wilcoxon signed-rank test. In variation analyses of several groups ANOVA and ANCOVA will be used. A significant difference of p-values below 0.05 has to be determined, to determine the validity of the findings. With a significant level of 5% a power calculation estimated a needed sample size of 14 patients, with a power of 90%. The calculation is based on an expected decrease in muscle volume compared to fat (1.2 vs 0.95 with a standard deviation of 0.2). The power calculation is an estimate, but compared to a similar study^xiii^ the sample size includes an extra 3 subjects. Given the rare condition of PD, inclusion of patients will continue even if the required minimum is achieved.

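### The unpaired t-test named for comparing baseline with visits allows the 6-month values of de novo Pompe patients to be set against the baseline of the whole mixed cohort

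*Protocol*

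**What the plan says.** Under Study population, the protocol plans two examinations for all Pompe patients: "Patients will be evaluated at inclusion and again after 10 months". A third applies to a subset: "In case of de novo patients an additional examination date will be performed following 6 months of treatment". Its purpose is stated directly afterwards: "This will provide detailed new results of muscle structure and function in the early stages of treatment, before and after initial ERT".

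The cohort is mixed by design. Danish patients are invited "irrespective of whether they are given ERT or not", and the planned size is 15 Pompe patients with 15 controls. The number of de novo patients expected is not given.

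The Statistics section has one sentence on longitudinal comparisons: "Comparison between baseline and visits will be performed using conventional statistic methods as unpaired t-test or non-parametric tests such as Wilcoxon signed-rank test". The first test named is for independent samples; the second is for paired data. The sentence does not say which patients enter the comparison at each visit. ANOVA and ANCOVA are mentioned separately, for analyses across several groups.

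**The concern.** The month-10 visit and the de novo month-6 visit are the only follow-up examinations described for Pompe patients, so the plural in the Statistics sentence most naturally covers both. Membership differs between them: all 15 patients at inclusion, only the k de novo patients at month 6, and all 15 again at month 10.

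A paired test cannot use a patient who lacks one of the two measurements. An unpaired t-test can, and it would run on 15 baseline values against k month-6 values without any warning. If newly treated patients differ at baseline from long-treated or untreated ones, that difference would be reported as change after six months of treatment. The early course of treatment is what the extra visit is meant to show, and the Aim includes muscle quality before and after enzyme replacement therapy (ERT).

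A second point concerns interpretation. The 6-month visit counts from the start of treatment and the 10-month visit from inclusion. Even with correct pairing, a de novo month-6 change and an all-patient month-10 change describe different patients on different clocks.

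**Working it through.** **Inputs from the protocol.** Planned N = 15 Pompe patients (Study population). Ratio means 1.2 and 0.95, so a planning difference of 0.25; SD 0.2; 5% significance level; 90% power; required size 14 (Statistics).

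**Inputs assumed, because the protocol does not give them.** k = number of de novo patients; G = baseline gap in the muscle-to-fat ratio between de novo and other Pompe patients; r = within-patient correlation between visits.

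**Step 1: the plan's own figure.** For two independent groups, two-sided, normal approximation:

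n per group = 2 × (1.960 + 1.282)² × (0.2/0.25)² = 2 × 10.51 × 0.64 = 13.4, rounded up to 14.

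The stated 14 is therefore reproduced as a per-group number for two independent groups. Power at 14 per group is 91.1% by this approximation and 88.9% by the exact t calculation, which asks for 14.5, so 15 per group. The figure does not depend on the visit schedule and neither supports nor weakens the present point.

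**Step 2: composition shift at month 6, with no true change.** Let D be the mean in de novo patients and O the mean in the others.

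- All-patient baseline mean = (k/15) × D + (1 - k/15) × O
- De novo month-6 mean = D
- Apparent change = D - [(k/15) × D + (1 - k/15) × O] = (1 - k/15) × (D - O) = (1 - k/15) × G

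| Assumed G (ratio units; in SDs of 0.2) | k = 1 | k = 2 | k = 3 | k = 5 | k = 8 | k = 15 |
|---|---|---|---|---|---|---|
| 0.10 (0.5 SD) | 0.093 | 0.087 | 0.080 | 0.067 | 0.047 | 0 |
| 0.20 (1 SD) | 0.187 | 0.173 | 0.160 | 0.133 | 0.093 | 0 |
| 0.25 (1.25 SD) | 0.233 | 0.217 | 0.200 | 0.167 | 0.117 | 0 |

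Example: k = 3 and G = 0.20 give (1 - 3/15) × 0.20 = 0.160. If k = 0 there is no month-6 examination and nothing to compare.

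**Step 3: the same shift under other comparisons.** De novo month 6 against the same patients' inclusion values: D - D = 0. Inclusion against month 10: both visits are planned for all patients, so the shift due to the schedule is 0.

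**Step 4: what the unpaired test does when the patients are the same.** There is no composition shift, but the correlation is ignored. Simulation with 15 patients, SD 0.2 at both visits and an assumed change of 0.10:

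| r | Unpaired: type I error | Unpaired: power | Paired: power |
|---|---|---|---|
| 0.5 | 0.8% | 20% | 44% |
| 0.8 | 0.03% | 13% | 81% |

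The unpaired test is therefore unsuitable for either visit: it permits the wrong comparator at month 6, and it loses power wherever the same patients are compared.

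**Step 5: what a paired month-6 test could show.** For a change of 0.25, SD 0.2 and r from 0.5 to 0.8, power is 11% to 17% with k = 2, 24% to 46% with k = 3, and 56% to 90% with k = 5.

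**The case against.** The strongest reply is that the protocol nowhere plans the mismatched comparison. The stated purpose of the extra visit is a before-and-after look at initial treatment, and only de novo patients have a value before initial treatment, so a within-de-novo comparison is the natural reading. The Statistics sentence also names the signed-rank test, which enforces that reading. Inclusion and month 10 cover the same patients. The number of de novo patients may be zero or one, and analysis sets are commonly left to a statistical analysis plan.

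Most of this stands, and it limits the point. A reader might infer that the planned longitudinal comparison as a whole sets different patients against each other; it does not, because inclusion versus month 10 has the same members by design. A reader might also infer a treatment gain that falsely fades. For example, a sustained gain of 0.5 SD in de novo patients, with no change in the others, reads as 0.5 SD at month 6 and (k/15) × 0.5 = 0.07, 0.10 or 0.17 SD at month 10 for k = 2, 3 or 5. That appears only if the two changes are joined in one curve, which the protocol does not propose, and the month-10 figure is simply dilution of the effect in the mixed cohort. Nor is an ANOVA across visits planned.

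The reply does not remove the defect in the Statistics sentence. That sentence does more than leave detail open: it names an independent-samples test for repeated measurements and applies it to visits with different membership. Followed literally, it gives an unsound month-6 comparison, either by using the wrong baseline or by treating the same patients as independent.

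**Conclusion.** The point holds as a conditional risk created by a badly chosen test, not as a stated plan to compare different patients. If the whole-cohort baseline were used as comparator, the spurious month-6 shift would be (1 - k/15) × G: 0.07 to 0.23 ratio units for k = 1 to 5 and G = 0.10 to 0.25. At the upper end this approaches the planning difference of 0.25. These sizes are illustrative, because k and G are assumptions and the planned 15 patients are taken as enrolled. The shift is zero when the same patients are compared, and there is no month-6 comparison if no de novo patient enters. Inclusion versus month 10 carries no shift from the schedule, although an unpaired test would still be the wrong choice there.

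**What to change.** Change the Statistics section to state four things:

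1. Comparisons of baseline with a visit use a within-patient method (for example a paired t-test or the signed-rank test), in place of the unpaired t-test.
2. Month-6 values are compared only with the same de novo patients' own inclusion and 10-month values, with the number of patients given and individual values shown if they are few.
3. The all-patient longitudinal comparison uses inclusion and month 10.
4. The de novo month-6 change and the all-patient month-10 change are not read as one time course, since one counts from the start of treatment and the other from inclusion.

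The cost is wording; no visit, measurement or patient is added. The drawback is that month-6 results will rest on a few patients and should be presented as descriptive, as the power figures for k = 2 or 3 show.

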**MR protocol**

The MR protocol includes the special T1 weighted sequence DIXON (1x1x3mm^3^; TR: 5.31ms TE: 2.46ms) enabling acquisition of muscle and fat images at 3 Tesla (Magnetom-Skyra, Siemens AG, Erlangen, Germany). The MR scans will consist of 400 axial slices covering from L1 to the ankle resulting in a total scan time of 22½ minutes.

[figure not shown]

**FIGURE 1 – A) FAST VIEW WHOLE-BODY CORONAL SCAN, RED LINE INDICATES THE REGION-OF-INTEREST FROM L1 TO THE ANKLE, USED IN THE DIXON SCAN. B) DIXON SCAN OF THIGH IN HEALTHY SUBJECT. C) SEGMENTATION OF MUSCLE, FAT AND BONE MARROW. D) VOLUMETRIC MODELLING OF MUSCLE, FAT AND BONEMARROW (RESULTS SEEN IN TABLE 2)**

**Isokinetic Dynamometry**

Muscle strength will be measured by isokinetic dynamometry. The measurement will be done using the Biodex System 3 PRO Dynamometer (Biodex Medical Systems Inc. NY, USA) for which a standardized protocol has been developed.

Maximal isokinetic strength of extensors and flexors of the dominating arm and extensor and flexors at the knee, ankle and hip of the non-dominant lower extremity will be measured.

**Risk, side effects and disadvantages**

There are no known side effects related to MR-scanning.
During the examination, the subjects will wear headphones in order to reduce the high sounds that comes from the scanning machine.
The scan is painless and there is no use of contrast. The only disadvantage is that the person has to lie still for 20-30 minutes.
There are some security rules to respect in order to avoid accidents due to metals being attracted by the machine’s strong magnetic field.

No side effects are associated to muscle strength measurement with the Dynamometer.
However, weak patients may be a bit tired after the examination, as they have to perform some movements using all their force.

**Statistics**

Comparison between baseline and visits will be performed using conventional statistic methods as unpaired t-test or non-parametric tests such as Wilcoxon signed-rank test. In variation analyses of several groups ANOVA and ANCOVA will be used. A significant difference of p-values below 0.05 has to be determined, to determine the validity of the findings. With a significant level of 5% a power calculation estimated a needed sample size of 14 patients, with a power of 90%. The calculation is based on an expected decrease in muscle volume compared to fat (1.2 vs 0.95 with a standard deviation of 0.2). The power calculation is an estimate, but compared to a similar study^xiii^ the sample size includes an extra 3 subjects. Given the rare condition of PD, inclusion of patients will continue even if the required minimum is achieved.

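### The tests named for baseline-versus-visit comparisons do not serve the before/after-ERT aim in a small de novo group: the unpaired t-test ignores pairing, and the signed-rank test may be unable to reach p<0.05

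*Protocol*

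**What the plan says.** The protocol's Aim section includes evaluating muscle quality in late-onset Pompe patients before and after ERT. The Study population section plans 15 Pompe patients, seen at inclusion and again after 10 months. On recruitment it says: "All patients with PD in Denmark (9) will be invited to participate, irrespective of whether they are given ERT or not". Patients who start treatment during the study appear only conditionally: "In case of de novo patients an additional examination date will be performed following 6 months of treatment". No number is given for them.

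For comparisons between baseline and visits, the Statistics section names an unpaired t-test or "non-parametric tests such as Wilcoxon signed-rank test". It then adds: "A significant difference of p-values below 0.05 has to be determined, to determine the validity of the findings". It does not say which test applies to which comparison or whether tests are two-sided.

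**The concern.** A before/after-ERT comparison needs a study measurement before treatment begins. Patients already on ERT at inclusion cannot supply one, and patients who never start ERT cannot supply the second measurement. The comparison therefore rests on the de novo patients, who may be few.

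Both tests named for baseline versus visits have a problem in that group. The unpaired t-test treats two measurements on the same patient as if they came from different people. The signed-rank test does respect the pairing, but with very few pairs its smallest attainable p-value lies above 0.05. Under the stated validity criterion, a before/after-ERT result could be set aside even if every patient changed strongly in the same direction. That result carries a stated aim. It also bears on the third hypothesis, that intrinsic strength reveals ERT effects better than the six-minute walk test.

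**Working it through.** **1. Sidedness, from the plan's own sample size.** The Statistics section says "With a significant level of 5% a power calculation estimated a needed sample size of 14 patients", at 90% power, for "1.2 vs 0.95 with a standard deviation of 0.2". The difference is 0.25 and the SD 0.2. With n = 2(z_α + z_β)² × SD²/difference² and SD²/difference² = 0.04/0.0625 = 0.64:

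- two-sided: 2 × (1.960 + 1.282)² × 0.64 = 13.4, so 14 per group
- one-sided: 2 × (1.645 + 1.282)² × 0.64 = 11.0, so 11 per group

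Of these two, only the two-sided calculation gives 14, so two-sided testing is the reading the document supports. The calculation reproduces as a two-group comparison. It does not address a before/after change in de novo patients.

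**2. Number of de novo patients.** Not stated. The inputs that bear on it are 9 Danish patients invited whether treated or not, 15 planned in total, and a research year from 1 September 2015 to 31 August 2016. If the 10-month visit must fall inside that year, about 2 months remain for enrolment. Six de novo patients would be 6/15 = 40% of the planned cohort. Five or fewer is therefore plausible, but it is an assumption.

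**3. Floor of the signed-rank test.** If all n changes have the same sign, with no ties or zeros, the exact two-sided p is 2/2ⁿ and the exact one-sided p is 1/2ⁿ.

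| Pairs | Exact two-sided | Exact one-sided | Normal approx., uncorrected | Normal approx., continuity-corrected |
|---|---|---|---|---|
| 3 | 0.25 | 0.125 | 0.109 | 0.181 |
| 4 | 0.125 | 0.0625 | 0.068 | 0.100 |
| 5 | 0.0625 | 0.031 | 0.043 | 0.059 |
| 6 | 0.031 | 0.016 | 0.028 | 0.036 |

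For n = 5 the largest rank sum is 15, its null mean is 7.5 and its SD is √(5 × 6 × 11/24) = 3.71. Then z = 7.5/3.71 = 2.02 (p = 0.043) without correction and 7.0/3.71 = 1.89 (p = 0.059) with it.

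With three or four pairs, every version stays above 0.05. With five, the exact two-sided and continuity-corrected versions stay above it and the other two can pass. With all 15 Pompe patients the exact two-sided floor is 2/2¹⁵ = 0.00006.

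**4. Cost of ignoring the pairing.** With equal variances and baseline-visit correlation ρ, the true variance of the mean change is 2σ²(1 − ρ)/n. The unpaired test uses about 2σ²/n, so its standard error is too large by a factor of 1/√(1 − ρ): 2.24 at ρ = 0.8 and 3.16 at ρ = 0.9. Two-sided 5% power for a true change of 2 SD of the within-patient changes (normal data; unpaired figures by simulation, paired figures from the noncentral t):

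| Pairs | Unpaired, ρ = 0.8 | Unpaired, ρ = 0.9 | Paired t |
|---|---|---|---|
| 4 | 32% | 14% | 75% |
| 5 | 43% | 17% | 91% |

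The correlations and the 2 SD change are assumptions. The gap narrows as the correlation falls.

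**5. What the paired t-test gives at smaller effects.** At 1.25 SD of the changes its power is 24% with three pairs, 41% with four and 56% with five. The value 1.25 equals 0.25/0.2 from the Statistics section. That is a between-group ratio, used here only as an illustration.

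**The case against.** The strongest reply is that the protocol never assigns the signed-rank test to the de novo patients. It is an example on one side of an alternative, for visit comparisons in general, and a t-test has no floor. A reader might infer that the before/after-ERT comparison must fail by construction. The document does not support that: the failure needs someone to choose the test, and it needs a group size the document does not give. This stands. However, the t-test on offer is the unpaired one, so the other branch of the sentence does not rescue the comparison either.

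A reader might also infer that the signed-rank test can never reach 0.05 with five pairs. That is true only of the exact two-sided and continuity-corrected versions, and the protocol does not state sidedness. The claim is firm in every version only for four pairs or fewer.

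Three further replies have weight. The p<0.05 sentence may be no more than a clumsy statement of the significance level, and the Dissemination section commits to publishing inconclusive results, so a non-significant finding would still be reported. The choice between parametric and non-parametric tests in a small subgroup is commonly left to an analysis plan; but the protocol has itself named an unpaired test for within-patient data, and that is a misstatement, not a gap. Finally, a paired t-test is also weak in very small groups unless the effect is large, and its normality assumption cannot be checked there. The shortage of de novo patients is the main limitation, and no choice of test removes it.

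**Conclusion.** The point holds in a limited form. As written, the Statistics section offers two tests for baseline versus visits. The unpaired t-test is wrong for within-patient data. The signed-rank test is correctly paired, but in its exact two-sided form it needs at least six non-zero pairs before p<0.05 is possible.

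The consequence for the before/after-ERT aim depends on there being five or fewer de novo patients (assumed), on the version of the signed-rank test, and on how literally the validity sentence is taken. The power loss from ignoring pairing, 91% down to about 43% with five patients, depends on a correlation of 0.8 and a change of 2 SD, neither of which is in the document.

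A reader might infer that the whole follow-up analysis is blocked. It is not: the inclusion-to-10-month comparison in all 15 Pompe patients is untouched by the floor, although the unpaired t-test is equally unsuitable for it. Nor does a paired t-test make the de novo comparison well powered.

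**What to change.** In the Statistics section:

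- Replace the unpaired t-test for baseline-versus-visit comparisons with a paired analysis of within-patient change: a paired t-test, on the log or percent scale if changes are skewed.
- State that the de novo before/after-ERT result is reported as mean change with a 95% CI and each patient's values, and is not judged by p<0.05 alone.
- If a signed-rank test is also used, note that its exact two-sided form cannot reach p<0.05 with fewer than six pairs. An outright ban below six pairs is not needed; that would be partly a matter of preference.

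This costs a few sentences and no new data. The downside is that a t-interval from three to five patients relies on roughly normal changes and will be wide, with only moderate power at smaller effects.

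### ANOVA/ANCOVA in their usual form assume one variance for patients and controls; separate-variance methods would protect the group comparisons if the spreads differ (minor)

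*Protocol*

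**What the plan says.** The Statistics section of the protocol names the method for comparing groups: "In variation analyses of several groups ANOVA and ANCOVA will be used". It does not say which groups enter one model, how pairwise contrasts are formed, or whether equal variances are assumed. The same section names "conventional statistic methods as unpaired t-test or non-parametric tests such as Wilcoxon signed-rank test", but for comparing baseline with later visits. Findings are judged at p below 0.05.

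On the groups, Study population states "Fifteen patients with PD and 15 healthy age matched control subjects will be included" and adds fifteen patients with myotonic dystrophy. Pompe patients enter whether or not they receive enzyme replacement. The Aim section asks for each disease to be compared with healthy controls and for the two diseases to be compared with each other.

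On spread, the only figure is the single SD in the sample-size basis: "1.2 vs 0.95 with a standard deviation of 0.2". In words, the background says of Pompe disease that "The disease presents in a wide range of phenotypes" and, of treatment studies, that "the studies underline the heterogeneity of clinical manifestation of disease and of ERT outcome".

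**The concern.** Ordinary ANOVA estimates one residual variance from all groups and uses it for every contrast. If the patient groups are more variable than controls, the pooled value is too small for the contrast between the two diseases and too large for patient versus control. Equal group sizes do not cure this, because a contrast between two groups borrows its error from a third.

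Unequal spread is plausible here. The Pompe group mixes treated and untreated patients with a disease that the protocol calls variable. The second hypothesis expects fat replacement to follow disease grade in both diseases, a source of spread that healthy controls lack. At stake is the error rate of comparisons that are stated aims, and some power for patient versus control.

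**Working it through.** **The plan's own figure.** Two-sided 5%, 90% power, difference 1.2 − 0.95 = 0.25, common SD 0.2:

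n per group = 2 × (1.960 + 1.282)² × (0.2/0.25)² = 2 × 10.51 × 0.64 = 13.45, rounded up to 14.

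This matches the stated 14 if read as 14 per group. The present point does not alter it.

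**Inputs.** From the protocol: 15 per group and a 5% level. Assumed: two-sided tests, normal data, all three groups in one model, pairwise contrasts using the pooled error on 45 − 3 = 42 degrees of freedom, and the SD ratios. The documents give no group-specific SD, so a range is shown.

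**Mechanism.** With equal n, the pooled variance estimates (σ²C + σ²P + σ²D)/3, for controls (C), Pompe (P) and myotonic dystrophy (D). A contrast of groups i and j needs (σ²i + σ²j)/2. The ratio of needed to pooled variance shows the direction: above 1 is liberal, below 1 conservative. Take control SD = 1.

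- Both patient SDs 2: pooled (1 + 4 + 4)/3 = 3. Pompe versus myotonic dystrophy: 4/3 = 1.33. Patient versus control: 2.5/3 = 0.83.
- Both patient SDs 0.5: pooled (1 + 0.25 + 0.25)/3 = 0.5. Pompe versus myotonic dystrophy: 0.25/0.5 = 0.5. Patient versus control: 0.625/0.5 = 1.25.
- Only Pompe SD 2: pooled (1 + 4 + 1)/3 = 2. Both Pompe contrasts: 2.5/2 = 1.25.

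**Simulated error rates** (200,000 trials per row, all means equal, nominal 5%):

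| SD pattern (C : P : D) | Pompe vs myotonic dystrophy | Pompe vs control | Overall F |
|---|---|---|---|
| 1 : 1 : 1 | 5.0% | 5.0% | 5.0% |
| 1 : 1.5 : 1.5 | 7.7% | 3.9% | 5.4% |
| 1 : 2 : 2 | 8.8% | 3.4% | 5.5% |
| 1 : 3 : 3 | 10.0% | 3.0% | 6.0% |
| 1 : 0.5 : 0.5 | 0.8% | 8.2% | 6.2% |
| 1 : 2 : 1 | 8.3% | 8.2% | 6.3% |

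Welch pairwise tests stay at 4.8–5.1% in every row.

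**Testing contrasts only after a significant F.** With all means equal, this holds Pompe versus myotonic dystrophy at 4.6% (ratio 2) and 5.4% (ratio 3). It protects little when patients truly differ from controls. With controls at 1.2, both patient groups at 0.95 (the same mean for myotonic dystrophy is an assumption), and control SD 0.15, the error is about 8% at patient SD 0.25 and about 9% at patient SD 0.30.

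**Power for patient versus control.** With all SDs 0.2: 91.7% pooled, 91.0% Welch. With SDs 0.126 (controls) and 0.253 (patients), whose variances average (0.0159 + 0.0640)/2 ≈ 0.04 = 0.2²: 88.3% pooled, 90.3% Welch.

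**The case against.** The strongest reply is that the protocol does not commit to the procedure that causes the harm. It does not mention a three-group model or a pooled error for pairwise contrasts. Welch ANOVA and ANCOVA with group-specific variances would both fit the quoted sentence, and such detail is commonly left to an analysis plan, which is not at hand. A two-group t-test of the two diseases with controls left out holds 4.9–5.1% when the two patient SDs are equal. All of this stands, and it is why the point is minor.

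The evidence for unequal spread is also only qualitative. The phenotype statement covers the whole disease, including the infantile form, whereas the study enrols adults. The other statement concerns clinical manifestation and treatment response, not the muscle-to-fat ratio. Neither describes myotonic dystrophy. Controls are matched on age alone and recruited by public notice. With fat in the denominator of the ratio, they could even be the wider group.

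A reader might therefore infer that the comparison of the two diseases is too liberal and that its true error is well above 5%. The documents do not support that. The only SD given is a common 0.2, at which every test holds 5%, and the direction reverses if controls vary more.

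What the reply does not remove is that the usual form of the named method depends on equal variances, which the protocol gives no reason to expect. In each unequal-variance pattern in the table, at least one stated comparison exceeds 5%.

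**Conclusion.** The point holds conditionally and is minor. If variances differ between groups and pairwise contrasts use the pooled three-group error, individual comparisons have error rates from about 0.8% to about 10% over the assumed SD ratios of 0.5 to 3. Which comparison is liberal depends on which group is wider, and the protocol does not settle that. With equal group sizes the overall F-test is only mildly affected. The conclusion rests on assumed SD ratios, normal data, 15 per group and the ordinary form of ANOVA. It establishes no error in the plan and leaves the sample size of 14 untouched. It is worth acting on because one sentence secures the 5% level whichever way the variances differ.

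**What to change.** In the Statistics section, state that comparisons across controls, Pompe disease and myotonic dystrophy use Welch ANOVA with Welch pairwise tests, and that ANCOVA is fitted with group-specific residual variances or HC3 standard errors. If an analysis plan exists, the sentence can go there instead, with the same wording for both analyses.

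The cost is one sentence and standard software. If the variances are in fact equal, the loss is 91.7 − 91.0 = 0.7 percentage points of power at the planning values with 15 per group.
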